## Abstract

Increasingly the value of gestational weight gain (GWG) as a useful measure to predict obstetric outcomes including cesarean section is being questioned. We will undertake a retrospective cohort study of recorded births in 2023 from 24 to 42 weeks’ gestation for women aged from 16 to 49 years in the United States. Using multivariable Robust Poisson Regression, maternal body mass index (BMI) and BMI gain will be modelled on the primary outcome of cesarean delivery. The primary analysis will be restricted to nulliparous women if there is interaction between parity and BMI or BMI gain. A sample of 716,392 births will be required to show approximately a one percentage point increase in cesarean section for each BMI classification compared with normal BMI (18.5 to <25) or per unit gain in maternal BMI. We hypothesize that the risk of cesarean section will increase with an increase in the BMI category and that BMI at birth may be a more relevant predictor of cesarean section than pre-pregnancy BMI. This question is important to answer given recent evidence casting doubt on the association between excessive GWG, which has been the focus of most interventions (with modest impact at best), and adverse pregnancy outcomes.

## Specifications table

**Table utbl0001:** 

**Subject area**	Medicine and Dentistry
**More specific subject area**	Maternal obesity
**Name of your protocol**	The association between gestational body mass index change, cesarean section, and other pregnancy outcomes: Research Protocol: Retrospective Cohort Analysis
**Reagents/tools**	N/A
**Experimental design**	Retrospective cohort study
**Trial registration**	*N/A*
**Ethics**	Ethics approval was not required nor sought from any ethical committee, as publicly available de-identified data were used.
**Value of the Protocol**	*This protocol*

## Background

As of 2021, the worldwide average cesarean section rate was 21 %, and is predicted to increase to 30 % by 2030 [1]. In 2022, 39 % of babies in Australia and 32.1 % in the United States (US) were born by cesarean delivery [2,3]. Occurring in parallel is the obesity epidemic, with 61 % and 69 % of women in Australia and the US, respectively, living with overweight or obesity [4]. Obesity is a major risk factor for cesarean section, and higher risk of complications of the surgery including wound infection and longer hospital stay [5,6]. Cesarean delivery is in turn associated with greater risk for mothers and babies including maternal death, severe postpartum haemorrhage, endometritis [7,8], as well as complications for future pregnancies, such as preterm birth and abnormal placentation [9].

Interventions to reduce perinatal complications have focused on gestational weight gain (GWG), with studies linking it to adverse pregnancy outcomes, including cesarean delivery [[10], [11], [12]]. Excessive GWG is defined according to prepregnancy body mass index (BMI) by both the National Academy of Medicine (NAM) and the World Health Organization with lower GWG recommended for those starting pregnancy with a BMI in the obese category compared to those with normal BMI at the start of pregnancy [13,14]. Studies to date have included adjustment for pre-pregnancy or early pregnancy BMI, but, it is unknown whether this association could in fact be mediated by increased BMI at the time of delivery. Recently there has been some questioning of the value of GWG as a useful measure to predict obstetric outcomes. In a study by Dodd et al that used data from 20 randomized controlled trials, the authors identified a meaningful relationship between maternal BMI and GWG, whereby GWG decreased with increasing BMI. They also demonstrated a relationship between BMI and adverse pregnancy outcomes, whereby the risk of adverse pregnancy outcomes increased with increasing maternal BMI. However, they found no evidence that the effect of maternal BMI on outcomes is via an effect on GWG. That is, gestational weight gain may not be associated with cesarean delivery independently of BMI at the time of birth [16].

Given that finding, in this research we sought to explore whether using gestational BMI change is a better measure to use in understanding adverse obstetric outcomes. The primary objective of this study is to describe the relationship between gestational BMI gain and cesarean delivery and to compare pre-pregnancy BMI versus BMI at the time of birth as predictors of cesarean delivery.

## Description of protocol

### Method

**Study Design:** This will be a retrospective cohort study examining the relationship between gestational BMI change and the rate of cesarean section. The study will be reported according to STROBE Guidelines[17].

**Study Setting:** Eligible births recorded by the Center for Disease Control and Prevention 2023 Natality File, USA.

### Participants

#### Inclusion criteria

Inclusion criteria will include:-Registered births in the United States in 2023 at 24 to 42 weeks’ gestational age at birth

#### Exclusion criteria

Exclusion criteria will include:-Stillbirths (as the stillbirth dataset does not include maternal weight at delivery)-Multiple pregnancies-Non-cephalic presentations-Previous cesarean delivery-Maternal age < 16 years or maternal age > 49 years

### Primary study factors

-Change in maternal BMI from pre-pregnancy to birth-Maternal BMI (either pre-pregnancy BMI or BMI at birth as outlined below)

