### Secondary outcomes

Secondary outcomes were clinically relevant outcomes available in the dataset.

Maternal
-Third- or fourth-degree perineal laceration-Instrumental vaginal delivery-Diabetes in pregnancy (pre-existing type 1 or type 2 diabetes or gestational diabetes)-Pre-term delivery-Hypertensive disorders in pregnancy-Induction of labour-Augmentation of labour-Chorioamnionitis in labour-Unplanned hysterectomy-Blood transfusion-Admission to intensive care unit (ICU)-Trial of labour

Neonatal
-Birth weight >90th percentile-Birth weight <10th percentile-Apgar Score < 6 at 5 min-Assisted Ventilation immediately following delivery-Assisted ventilation required for more than 6 h-Neonatal intensive care unit (NICU) admission-Antibiotics received for suspected neonatal sepsis-Seizure or serious neurological dysfunction-Infant breastfed at discharge

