As nulliparous women are an important group who contribute to the first/primary cesarean delivery rate, we will test for interaction (effect modification) between maternal BMI gain and parity, and maternal BMI and parity. If interaction is present (BMI or BMI gain have a different association with cesarean delivery depending on parity), then the primary analysis will be restricted to nulliparous women only and we will conduct secondary analyses for parous women.

For the primary outcome of cesarean delivery, backward stepwise Robust Poisson Regression will be used. The following variables will be included in the multivariable Poisson regression model as potential predictors of cesarean section:•Maternal BMI (not eligible for exclusion in the backwards stepwise regression).•Gestational BMI gain (not eligible for exclusion in the backwards stepwise regression)•Parity•Maternal age (continuous)•Gestational age•Maternal height•Maternal race•Cigarette smoking•Payment type•Trimester of onset of maternity care (4 categories: first, second or third trimester, or no•antenatal care)•Education (categorized)•Fertility treatment used•Diabetes (3 categories: pre-pregnancy, gestational, none)•Hypertension in pregnancy (dichotomous)•Interaction terms: BMI x parity and BMI gain x parity

Birthweight will not be included as an explanatory variable because it was considered that fetal weight may be on the causal pathway between BMI or BMI gain and cesarean delivery. Therefore, the relative risks for BMI or BMI gain for the primary outcome of cesarean delivery will include any indirect effect mediated through fetal weight.

If Robust Poisson Regression Models do not converge then alternative regression methods will be considered.

For secondary outcomes, all explanatory variables will be retained in the model. Stepwise backward regression will not be used. No interaction terms will be used.

For the secondary outcome of third or fourth degree perineal laceration, the data will be limited to vaginal births only and the following covariates will be used: BMI at delivery, BMI gain, parity, maternal age, gestational age, maternal height, maternal race, mode of delivery (unassisted/vacuum/forceps).

For the secondary outcome of trial of labour, the following covariates will be used: BMI at delivery, BMI gain, parity, maternal age, gestational age, maternal height, maternal race, payment type, education, trimester of onset of maternity care, use of ARTs, and gestational diabetes.

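### Diabetes and hypertensive disorders in pregnancy would be modelled on BMI gain completed after they arise, so their gain relative risks are open to reverse causation of unknown size and direction

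*Protocol article*

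**What the plan says.** Under Primary study factors, the protocol article names two exposures: "Change in maternal BMI from pre-pregnancy to birth" and "Maternal BMI (either pre-pregnancy BMI or BMI at birth as outlined below". The Variables section lists pre-pregnancy BMI, BMI at birth, BMI gain and weight gain. It lists no weight at booking, at diagnosis or at any other point in pregnancy.

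Under Secondary outcomes, the maternal list includes "Diabetes in pregnancy (pre-existing type 1 or type 2 diabetes or gestational diabetes" and "Hypertensive disorders in pregnancy".

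The Analysis plan chooses between pre-pregnancy and delivery BMI by AIC in the cesarean models and carries the winner into later analyses. It forces gain into the primary model: "Gestational BMI gain (not eligible for exclusion in the backwards stepwise regression". It then states: "For secondary outcomes, all explanatory variables will be retained in the model". Separate covariate instructions follow for perineal laceration, trial of labour, preterm birth, NICU admission and a group of rare outcomes. None is given for diabetes or hypertensive disorders.

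The same conditions also stand on the list of explanatory variables, as "Diabetes (3 categories: pre-pregnancy, gestational, none" and "Hypertension in pregnancy (dichotomous".

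**The concern.** An exposure should be complete, or at least measurable, before the outcome it is meant to explain. Here the exposure window closes at delivery, while the two outcomes are present or arise before then. Any gain that accrues after onset could be altered by the condition or by the response to it, and would still be counted as exposure. The regression cannot tell gain that preceded the disease from gain that followed it.

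This matters because of how the results would be used. The Background section asks whether gestational BMI change is a better measure for understanding adverse obstetric outcomes. The section on the study's uniqueness links the findings to resource allocation and to expectations about limiting gain. A gain relative risk for diabetes or hypertension would be read in that light. With a required sample above half a million births, any artefact could also carry a very narrow confidence interval. The Limitations section discusses misreported weight in relation to cesarean delivery and does not mention time order.

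**Working it through.** **Step 1: time order, from the text.** No figure in the protocol needs reproducing; the point rests on setting the sections side by side.

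| Condition | When it begins | Gain exposure ends | Order |
|---|---|---|---|
| Pre-existing type 1 or type 2 diabetes | Before pregnancy | Birth | Outcome precedes all of the gain |
| Gestational diabetes | During pregnancy | Birth | Outcome generally precedes part of the gain |
| Hypertensive disorders in pregnancy | Generally during pregnancy | Birth | Outcome generally precedes part of the gain |

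Delivery BMI, if selected, is also measured after onset. Pre-pregnancy BMI has no such fault for the pregnancy-onset conditions.

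**Step 2: does gain enter these two models?** No model is written out for either outcome, so this is read from the general rule. Two features support the reading. Gain is a primary study factor, and it appears in both secondary models whose covariates are spelled out in full (perineal laceration and trial of labour). Taken literally, the rule would also place each condition among the covariates of its own model, so it needs an exception in any case.

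**Step 3: illustration of size. All inputs are assumed; none is in the documents.** Suppose gain has no effect on the outcome, but cases have their later gain shifted by d kg/m². For a roughly normal exposure with standard deviation σ and outcome prevalence p:

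log RR per kg/m² ≈ (1 − p) × d / σ²

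- Set A, p = 0.10 and σ = 2.25 (σ² = 5.06):
  - d = +0.5 gives 0.90 × 0.5 / 5.06 = 0.089, RR 1.09
  - d = −0.5 gives RR 0.91
  - d = +1.0 gives RR 1.19
- Set B, p = 0.08, early and late gain each with SD 1.2 (total σ² = 1.44 + 1.44 = 2.88):
  - d = +0.5 gives 0.92 × 0.5 / 2.88 = 0.160, RR 1.17

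A simulation of set B with 300,000 births and robust Poisson regression gave 1.17, 0.85 and 1.37 for d = +0.5, −0.5 and +1.0. The relative risk for gain before onset stayed at about 1.00, and with d = 0 both relative risks were about 1.01. The two sets agree on the mechanism and differ mainly through the assumed σ.

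**Step 4: precision.** With the protocol's required full-sample size of 570,014 and set A, the standard error of the log RR is about 1 / (2.25 × √(570,014 × 0.10)) = 1 / (2.25 × 238.8) = 0.0019, ignoring covariates. An artefact of 0.089 would then have a 95% interval of about 1.089 to 1.097.

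**The case against.** The strongest reply has four parts.

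- **The models are inferred.** This stands as a caution. The general rule cannot be applied literally to these outcomes, so some adaptation must be intended, and a condensed article may not show it. But the rule is stated positively, gain is a main study factor, and exceptions are written for other outcomes and not for these.
- **The aim is descriptive.** The primary objective is to describe a relationship, and the word predictors is used only for cesarean delivery. That softens any charge that the protocol claims causation. It does not make the association interpretable. The authors do reason about causal position elsewhere: they leave out birthweight as a possible mediator and drop gestational age from the preterm model.
- **It is a data constraint, and labelling would do.** The Limitations section concedes that administrative data restrict the available variables. A label would help, but the headline estimate would still be one that cannot be read as an effect of gain, while a properly ordered alternative is available from the same file.
- **The reach is small.** Two of 21 listed secondary outcomes are affected. This stands.

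A reader might go further and infer that weight change caused by the disease will in fact be reported as a predictor of it. The documents do not support that. They show the time order only; they contain nothing on whether, how far or in which direction weight changes after onset. Nor should the per-unit illustrations be stretched over a 5 kg/m² contrast: they assume one linear slope, whereas the protocol models gain as a spline with a knot at 5 kg/m².

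**Conclusion.** The concern holds as a matter of design. Under the stated rule, the gain relative risks for diabetes and hypertensive disorders, and the delivery BMI relative risks if that variable is selected, are open to reverse causation of unknown size and direction. Pooling pre-existing with gestational diabetes makes the time order worse, because pre-existing disease precedes all of the gain. Restricting the outcome to gestational diabetes would not be enough alone, because the exposure would still run past onset.

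The figures of roughly 1.09 to 1.17 per kg/m² for a 0.5 kg/m² upward shift, and 0.85 to 0.91 for a downward one, depend wholly on the assumed shift, standard deviation and prevalence. They show that a spurious association of either sign can arise with no true effect; they do not estimate the bias in this study. The conclusion also rests on the general rule governing these two outcomes. Cesarean delivery, the sample size and the choice of BMI variable are not affected. The change should be made, but it is not critical to the primary result.

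**What to change.** **Analysis plan.** State that, for gestational diabetes and for hypertensive disorders, the reported model uses pre-pregnancy BMI whatever the AIC step selects, excludes gestational BMI gain, and excludes the outcome condition from its own covariates.

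**Secondary outcomes.** Separate gestational from pre-existing diabetes and make gestational diabetes the modelled outcome. The three-category diabetes covariate already assumes that the file allows this split. Say how women with pre-existing diabetes are handled in that model.

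**Reporting.** If gain is shown for these outcomes, present it as a description of gain by disease status, labelled as not time-ordered and open to reverse causation. Add a sentence to the Limitations section to the same effect.

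**Cost.** A few sentences in three sections and no new data. Two secondary outcomes lose a gain relative risk, but one that could not have been interpreted. The pooled diabetes outcome is replaced by a narrower one. The primary analysis is untouched.

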### Primary outcome

Rate of cesarean delivery

### Secondary outcomes

Secondary outcomes were clinically relevant outcomes available in the dataset.

Maternal
-Third- or fourth-degree perineal laceration-Instrumental vaginal delivery-Diabetes in pregnancy (pre-existing type 1 or type 2 diabetes or gestational diabetes)-Pre-term delivery-Hypertensive disorders in pregnancy-Induction of labour-Augmentation of labour-Chorioamnionitis in labour-Unplanned hysterectomy-Blood transfusion-Admission to intensive care unit (ICU)-Trial of labour

Neonatal
-Birth weight >90th percentile-Birth weight <10th percentile-Apgar Score < 6 at 5 min-Assisted Ventilation immediately following delivery-Assisted ventilation required for more than 6 h-Neonatal intensive care unit (NICU) admission-Antibiotics received for suspected neonatal sepsis-Seizure or serious neurological dysfunction-Infant breastfed at discharge

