For the secondary outcome of preterm birth, the same covariates will be used as for the primary outcome except gestational age will be removed and previous preterm birth will be added.

For the secondary outcome of NICU admission, the same covariates will be used as for the primary outcome of cesarean delivery.

For the uncommon or rare secondary outcomes of unplanned hysterectomy, maternal admission to the ICU, 5 min Apgar Score < 4, assisted ventilation immediately following delivery and for more than six hours, antibiotics for suspected neonatal sepsis, and neonatal seizure or serious neurological dysfunction, the same covariates will be used as for the primary outcome, if there are at least five events per variable. If there are fewer than five events per variable, then we will preselect a smaller group of the most relevant covariates or conduct a univariable analysis.

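### The diabetes secondary outcome includes disease that predates gestational BMI gain, and the covariate rule, read literally, puts diabetes and hypertension into their own models

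*Protocol article*

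**What the plan says.** Under Secondary outcomes, the protocol article lists "Diabetes in pregnancy (pre-existing type 1 or type 2 diabetes or gestational diabetes" and, as a separate item, "Hypertensive disorders in pregnancy". Under Primary study factors, the first exposure is "Change in maternal BMI from pre-pregnancy to birth"; the second is maternal BMI, either pre-pregnancy or at birth.

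The covariate list in the Analysis plan, introduced for the cesarean model, contains "Diabetes (3 categories: pre-pregnancy, gestational, none" and "Hypertension in pregnancy (dichotomous" as explanatory variables. The rule for the other outcomes is: "For secondary outcomes, all explanatory variables will be retained in the model". It goes on to rule out stepwise elimination and interaction terms.

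Outcome-specific covariate instructions follow for perineal laceration, trial of labour, preterm birth, NICU admission and a group of rare outcomes. The instruction on preterm delivery reads: "the same covariates will be used as for the primary outcome except gestational age will be removed and previous preterm birth will be added". No instruction is given for the diabetes or the hypertension outcome.

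**The concern.** There are two separate problems.

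**Timing.** Type 1 or type 2 diabetes that exists before conception cannot follow from BMI gained afterwards. Any association between gain and these cases must come from the disease or its management affecting gain, or from shared causes. Pooling them with gestational diabetes gives one relative risk for gain that describes neither group and cannot be read as gain preceding the outcome.

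**Covariates.** With no exception written, the general rule governs the diabetes and hypertension outcomes. Taken literally, each outcome then appears on the right-hand side of its own model. The three-level diabetes variable determines the composite outcome completely: no events in the level without diabetes, and an event for every woman in the other two levels. Nothing is left for BMI or BMI gain to explain.

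At stake is whether two of the 21 listed secondary outcomes (12 maternal, 9 neonatal) can be interpreted in relation to BMI gain.

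**Working it through.** The protocol states no figure on this point, so there is none to reproduce. The check is a comparison of the text, followed by an illustration on assumed inputs.

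**1. Text comparison**

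| Item | Diabetes | Hypertension | Preterm birth |
|---|---|---|---|
| Listed as secondary outcome | Yes, with pre-existing disease included | Yes, onset not specified | Yes |
| Overlapping variable in covariate list | Three-level diabetes | Binary hypertension | Gestational age |
| Written removal of that variable | None | None | Yes |

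The plan removes the overlapping variable for preterm birth and makes no matching removal for the other two. It can already separate the types of diabetes: the covariate has distinct pre-pregnancy and gestational levels, and the trial-of-labour model uses gestational diabetes alone.

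**2. Illustrative simulation (assumed inputs, not trial figures)**

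Robust Poisson regression, n = 200,000. Pre-existing diabetes about 1%, gestational diabetes about 7%. Residual SD of BMI gain 2 kg/m², and mean gain 1 kg/m² lower in women with pre-existing diabetes. The true relative risk of gestational diabetes per kg/m² of gain is exp(0.05) = 1.051.

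| Model | Relative risk per kg/m² of gain (95% CI) |
|---|---|
| Composite outcome, no diabetes covariate | 1.015 (1.008 to 1.022) |
| Gestational diabetes, pre-existing cases excluded | 1.054 (1.046 to 1.062) |
| Composite outcome with three-level diabetes covariate | 1.000; diabetes coefficients at relative risk about 10¹⁴ |

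In the last model the software still reported convergence. The failure shows in the coefficients, so the plan's fallback for non-converging models would not necessarily be triggered.

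**3. How far the first result depends on the assumptions**

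Let s be the share of composite events that are pre-existing, d the deficit in mean gain in those women, and σ the residual SD of gain. For a normal gain distribution shifted by d, the log relative risk of pre-existing disease per unit of gain is about −d/σ². To first order:

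log RR(composite) ≈ (1 − s) × 0.05 − s × d/σ²

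With s = 1/(1 + 7) = 0.125 and σ² = 4:

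- d = 1.0: 0.04375 − 0.03125 = 0.0125, RR 1.013 (simulation 1.015)
- d = 0.5: 0.04375 − 0.01563 = 0.0281, RR 1.029
- d = 0: 0.04375, RR 1.045
- d = −0.5 (higher gain in these women): 0.04375 + 0.01563 = 0.0594, RR 1.061

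Both the size and the direction of the distortion depend on d and s, and the protocol gives neither. If pre-existing diabetes were 1.0 to 1.5% and gestational diabetes 7 to 9%, s would run from 1.0/(1.0 + 9.0) = 10% to 1.5/(1.5 + 7.0) = 18%. These rates are also assumptions.

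**The case against.** The strongest reply is that self-inclusion is a drafting gap and not an intended analysis. The covariate list is introduced for cesarean section. The retention rule sits next to the sentence dropping stepwise elimination, so its purpose may be only to say that nothing is eliminated. The preterm exception shows that the authors know the principle, and an analyst would very likely remove an outcome from its own predictors. This stands. A reader might infer that the plan would wipe out the whole BMI and gain signal for these outcomes. That happens only if someone fits and reports a visibly degenerate model, and the document does not support treating it as a realistic result. What remains is a rule whose stated scope is wrong for two outcomes and needs one sentence.

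A second reply is that the study also relates outcomes to maternal BMI and describes its aim as describing relationships and comparing predictors. Diabetes of any type is a coherent outcome to relate to pre-pregnancy BMI. This also stands: the timing objection concerns the gain coefficient.

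Three further inferences are tempting and not supported:

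- That the hypertension outcome has the same timing fault. The protocol does not say whether chronic hypertension is counted, so only the covariate problem is shown there.
- That gestational diabetes alone is free of reverse direction. Gain is measured to birth and includes gain after a diagnosis during pregnancy.
- That these models must use pre-pregnancy BMI in place of whichever BMI measure the AIC comparison selects. That is a separate question, and this point does not settle it.

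The reply that an article condenses a fuller plan does not answer the timing problem. The article states the outcome definition in full, and it is the stated definition that is at fault.

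**Conclusion.** The point holds in two parts. First, the diabetes outcome as defined includes cases that predate the gain exposure, so its relative risk for gain cannot be read as gain preceding the outcome. This follows from the text alone. Second, the retention rule, read literally, places diabetes and hypertension in the models for those same outcomes; this is mainly a drafting error that would show itself on fitting.

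The size of the bias cannot be derived from the document. The move from 1.054 to 1.015 and the 10 to 18% share of events illustrate what assumed rates and an assumed gain deficit would produce; they are not estimates for this cohort. The cesarean analysis and the sample size are unaffected.

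**What to change.** 1. For the BMI-gain analysis, define the outcome as gestational diabetes among women without pre-existing diabetes, using the three-category variable already planned. If the any-diabetes composite is kept for description against maternal BMI, say so and report no gain relative risk for it.
2. Add an exception parallel to the one for preterm birth: the diabetes variable is removed from the diabetes model and the hypertension variable from the hypertension model. In the same sentence, state whether each condition stays in the other's model, since either may arise during pregnancy alongside gain.
3. Note that gain to birth includes gain after a gestational diabetes diagnosis, so the estimate remains an association.

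The cost is one outcome definition, one covariate sentence and one interpretive note. No new data are needed. Women with pre-existing diabetes leave this one analysis; their number is expected to be small, though the protocol gives no count.
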